### Criteria for discontinuing or modifying allocated interventions {11b}

Schools participate voluntarily in the program *Bullying&You* and are free to discontinue program implementation at any time. Pupils are free to leave the CRT (research study) at any time, for any reason, without any consequences. From the investigators’ side, there are no general criteria for discontinuing the intervention. Modification of the intervention may occur based on the continuous exchange with and feedback from the core teams regarding barriers that they come across during program implementation. For instance, some schools may not be able to provide the digital requirements for their pupils to complete the eLearning component of *Bullying&You*. In this case, these schools may entirely omit the eLearning for their pupils or the pupils may follow along the eLearning led by their teacher in class instead of completing it by themselves. To track these modifications, program fidelity of each school will be assessed by short teacher surveys at T1 and T2.

### Strategies to improve adherence to interventions {11c}

The systematic program structure helps the schools to plan the next steps and facilitates the implementation. To improve adherence in the IG, the research team meets the core team members of each school regularly (approximately every 2 months) and discusses the implementation of the specific program components. Furthermore, every couple of months, the core teams receive an email summarizing the next relevant steps in the program. Core teams are encouraged to contact the research team if any questions or issues occur. Additionally, the research team monitors the progress of each school’s teachers in completing the 6 eLearning units of the basic course and reports the proportion of completed units to the respective core team once a month. This helps the core team to develop strategies to motivate their teachers in case of low eLearning activity.

### Relevant concomitant care permitted or prohibited during the trial {11d}

Already established unsystematic or single anti-bullying efforts (such as a letter box to anonymously report bullying incidents) are permitted, but other whole-school bullying prevention programs than *Bullying&You* are prohibited during the trial.

### Provisions for post-trial care {30}

We do not anticipate any harms from trial participation. Therefore, there are no provisions for ancillary or post-trial care or for compensations.

### Outcomes {12}

#### First objective

The primary outcome of this trial is the reduction of bullying (prevalence of victims and perpetrators of direct, indirect, and cyberbullying within the last 6 months) assessed by the Bullying Screening [28, 29] from baseline (T0) to two annual follow-ups (T1 and T2) in the IG compared to the CG.

#### Second objective

Secondary outcome is the increase in general health-related quality of life within the last 7 days assessed by the KIDSCREEN-10 [30] in primary schools or KIDSCREEN-27 [31] in secondary schools from T0 to T1 and T2 in the IG compared to the CG.

For secondary schools, additional secondary outcomes are the reduction from T0 to T1 and T2 regarding the following mental health problems:Psychological distress within the last 6 months assessed by the Strengths and Difficulties Questionnaire (SDQ; [32])Self-harming behaviour within the last 12 and 3 months based on the Self-Injurious Thoughts and Behaviours Interview (SITBI; [33])Problematic Internet use within the last 12 months assessed by the Internet Gaming Disorder Scale (IGDS; [34]) and the Social Media Disorder Scale (SMDS; [35])

#### Third objective

To get insight into the effectiveness of specific components of the program, short surveys for teachers will be conducted at T1 and T2. Furthermore, the use of the eLearning platform is recorded continuously (i.e. the proportion of completed eLearning units).

#### Fourth objective

Individual characteristics predicting the program success at the individual level are obtained in secondary schools:Personality traits assessed by the Level of Personality Functioning Scale—Brief Form (LPFS-BF; [36])Internal self-blame assessed by the Attributions for Victimization Experiences Measure [37, 38]Callous-unemotional traits within the last 6 months assessed by the Inventory of Callous-Unemotional Traits—Youth Version (ICU; [39])

### Participant timeline {13}

The flowchart of the trial is shown in Fig. 3 and the schedule of enrolment, interventions, and assessments in Fig. 4.

**Fig. 3 Fig3:**
[figure not shown]
Consolidated Standards of Reporting Trials (CONSORT) 2010 flow diagram

**Fig. 4 Fig4:**
[figure not shown]
Schedule of enrolment, interventions, and assessments. SDQ, Strengths and Difficulties Questionnaire; IGDS, Internet Gaming Disorder Scale; SMDS, Social Media Disorder Scale; LPFS-BF, Level of Personality Functioning Scale—Brief Form; ICU, Inventory of Callous-Unemotional Traits—Youth Version

### Sample size {14}

To estimate the required sample size, Monte Carlo simulations were carried out using Stata 16.1 with the following assumptions: Two measurement points of 15 secondary schools per group with 10 classes per school and 5 primary schools per group with 4 classes per school are expected to take part in the study. In each class, 25 pupils are expected. Baseline bullying prevalence is estimated to be 15%, and the intervention is expected to lead to a relative reduction in bullying of 25%. The standard deviation (*SD*) of bullying rates between schools is *SD* = 0.2 on the logit scale; the *SD* of classes within schools is *SD* = 0.4 on the logit scale. This leads to an intraclass correlation coefficient on the school level of 0.011 and 0.057 on the class level. The assumptions were chosen so that the simulated data corresponded to the data from the OBPP study [18]. With these assumptions, 1000 data sets were simulated and analysed by three-level mixed logistic regression with group, measurement point, and their interaction as fixed effects and random intercepts on the school (level 3) and class (level 2) level. Using an alpha-error probability of 0.05, with 40 schools and 8500 pupils (4250 IG and 4250 CG) the power would be 86%.

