#### The challenges in bullying prevention

A recent meta-analysis including 100 independent evaluations of anti-bullying programs found that, overall, school-based programs were effective in reducing bullying perpetration and victimization [14]. The overall effect reported was a relative reduction of bullying between 15 and 20%, with wide variation in effect sizes between the single programs and studies [15]. While this is encouraging overall, there are several unresolved issues that need to be targeted by future developments of bullying prevention programs.

Another meta-analysis [16] revealed that the presence of two main intervention components was significantly correlated with effective reduction in school-bullying victimization, as well as perpetration outcomes: informal peer involvement and information for parents. Informal peer involvement refers to the use of in-class or group-based discussion, while information for parents was defined as providing parents with information about bullying-related issues through take-home letters or leaflets. Both components can only be covered in whole-school approaches which actively involve all actors within the school environment in anti-bullying activities. Thus, even if whole-school approaches are often related to more effort, they can most likely achieve far-reaching effects. In contrast, low-threshold programs are often not designed to be long-lasting and sustainable, so they do not result in any permanent changes in the school culture and bullying issues.

Many existing programs—in particular those applying whole-school approaches—are costly both in monetary terms as well as in expenditure of time, requiring high levels of training and staff commitment that is often reduced if programs are not tailored to the needs of the school staff [16, 17]. This results in a high threshold for the implementation of these programs. In line with this observation, our own evaluation of the Olweus Bullying Prevention Program (OBPP) in Germany—one of the most effective bullying prevention programs worldwide—resulted in a satisfactory bullying reduction of 25% after 2 years. However, enthusiasm was clearly diminished by the extremely low participation rate of schools during the recruitment and advertising phase (1.9%; [18]).

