## Methods: participants, interventions, and outcomes

### Study setting {9}

The study will be conducted at 30 secondary schools and 10 primary schools within the state of Baden-Wuerttemberg, Germany.

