### Recruitment {15}

The recruitment of secondary schools started in September 2021. A complete list of schools in the state of Baden-Wuerttemberg was acquired (public and private schools). For organizational reasons, only schools in two out of four regional councils in Baden-Wuerttemberg that met the eligibility criteria (912 secondary schools) were contacted by email and letter (addressed to principals and social workers). This contact contained our program flyer as well as an invitation to an information event, which took place in October 2021. In January 2022, schools received a reminder of the program by email. The step-by-step decision process of schools regarding their participation included the following: (1) Interested schools receive our detailed information folder, (2) followed by a digital meeting of a member of our research team with the school management and prevention team to clarify questions, and (3) a program presentation by a member of our research team at one of the school’s teacher conferences. In the end, teachers had to vote on the participation of their school in the program. In case of a positive vote, schools signed a participation agreement and were randomized to one of the two experimental conditions. Recruitment of secondary schools was stopped in December 2022 in order to stay within the timeline. Out of the targeted 30 secondary schools, 27 schools were recruited. Since three schools were missing, the number of primary schools was increased by three schools, resulting in a target of 13 primary schools. Thus, the overall target number of schools remained at 40.

Recruitment of primary schools started in September 2022 following an analogue approach. Four hundred and fifty-seven eligible primary schools (principals and social workers) were contacted by email and letter and invited to an information event, which took place in November 2022. Furthermore, 10 primary schools that belonged to a secondary school which already participated in the program were informed about the opportunity to join the program as well. In January 2023, the primary schools received a reminder of the program by email. Inclusion of primary schools was stopped in September 2023.

Recruitment of participants began in June 2022 and will be completed by October 2025.

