We orientated our expected effects on the effects of school-bullying prevention programs reported by the latest meta-analyses [14], but would nevertheless consider even smaller program effects as clinically meaningful, first because of the strong causal relationship of bullying experiences with the development of mental disorders [6–9], and second because of the resulting health care costs associated with bullying [43]. Given that this program aims at universal prevention of bullying and associated consequences for mental health, even small effects (i.e. slight changes in mean scores of mental health) can make meaningful contributions to prevalence rates and burden of disease [44].

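### The 86% power is for a 25% reduction matched to an earlier program's two-year result, while the protocol elsewhere says its expected effect follows meta-analyses it reports at 15 to 20%, where power is about 67% and 42%

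*Protocol article*

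**What the plan says.** **Sample size {14}.** The simulation assumes "Two measurement points of 15 secondary schools per group with 10 classes per school and 5 primary schools per group with 4 classes per school", and "In each class, 25 pupils are expected". It takes a 15% baseline prevalence, a 25% relative reduction, and logit-scale SDs of 0.2 (schools) and 0.4 (classes within schools). It says the assumptions were set to match the OBPP study data, and concludes that "with 40 schools and 8500 pupils (4250 IG and 4250 CG) the power would be 86" percent.

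**Background, The challenges in bullying prevention.** On the meta-analytic literature: "The overall effect reported was a relative reduction of bullying between 15 and 20" percent, with wide variation between programs. On the group's own OBPP evaluation: it "resulted in a satisfactory bullying reduction of 25% after 2 years".

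**Statistical methods {20a}.** "We orientated our expected effects on the effects of school-bullying prevention programs reported by the latest meta-analyses". The same sentence adds that effects below that level would still count as clinically meaningful.

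**Abstract, Methods.** The main endpoint is at one-year follow-up (T1). Objectives {7} and Outcomes {12} name both T1 and T2.

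**School numbers.** Recruitment {15} reports 27 secondary schools recruited out of 30 and a raised primary target, "resulting in a target of 13 primary schools. Thus, the overall target number of schools remained at 40". Study setting {9} still says "The study will be conducted at 30 secondary schools and 10 primary schools", the Discussion repeats that mix, and the Abstract and Sample size {14} still give 8500 pupils.

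**The concern.** Two sections give different origins for the expected effect, and the origins carry different numbers. The power calculation uses the OBPP figure of 25%. The methods section points to meta-analyses, which the background puts at 15 to 20%. A reader who combines the sections will take 86% as the power for the effect the protocol says it expects, which it is not.

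Timing adds to this. OBPP's 25% is a two-year result, the abstract's main endpoint is at one year, and the calculation uses two measurement points. The control schools start the program after one year, so T1 is the comparison in which they have not yet begun it.

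What is at stake is how a non-significant T1 result is read. With 86% power it would count as fair evidence against the expected effect. With power nearer one half to two thirds it would say much less.

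A smaller, separate matter is that the pupil total and the school mix were not updated when three primary schools replaced three secondary schools.

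**Working it through.** **Inputs (Sample size {14}).** Per group: 15 × 10 + 5 × 4 = 170 classes; 170 × 25 = 4250 pupils per wave; p0 = 0.15; class SD 0.4 (variance 0.16); school SD 0.2; alpha 0.05. Sidedness is not stated; two-sided is assumed.

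**Reproducing the plan's figures.**
- Pupils: 30 × 10 × 25 + 10 × 4 × 25 = 7500 + 1000 = 8500. Exact.
- ICCs, with residual variance π²/3 = 3.29: 0.04/3.49 = 0.0115 and (0.04 + 0.16)/3.49 = 0.0573. Both agree.
- Power for the group × time interaction on the logit scale. The school intercept cancels. With class effects drawn anew at each wave:

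  Var = Σ over four group-by-time cells of [1/(n p q) + 0.16/classes]

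  At a 25% reduction p1 = 0.1125:
  - three cells at 0.15: 3 × 1/(4250 × 0.1275) = 0.00554
  - one cell at 0.1125: 1/(4250 × 0.09984) = 0.00236
  - class term: 4 × 0.16/170 = 0.00376
  - Var = 0.01166, SE = 0.108
  - log odds ratio = logit(0.1125) − logit(0.15) = −0.331
  - z = 0.331/0.108 = 3.06; power = Φ(3.06 − 1.96) = 86.5%

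A Monte Carlo check with a fitted three-level logistic model gave 84.7% (300 runs). The stated 86% is reproduced.

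**The class-effect assumption.** The protocol does not say whether class effects persist between waves. If they are constant, the class term drops out and power at 25% is 96.1% (Monte Carlo 95.3%, 150 runs). If class and school effects are both redrawn, it is 65.5%. Among the two-sided interaction variants tried, only redrawing the class effects alone comes close to 86%.

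**Power at the effects named in the protocol, planned mix (8500 pupils).**

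| Reduction | log OR | SE | Power, class effects redrawn | Power, class effects constant |
|---|---|---|---|---|
| 25% | −0.331 | 0.1080 | 86.5% | 96.1% |
| 20% | −0.258 | 0.1074 | 67.0% | 83.3% |
| 15% | −0.189 | 0.1068 | 42.3% | 57.8% |

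**Revised mix.** 27 × 250 + 13 × 100 = 6750 + 1300 = 8050 pupils, in 27 × 10 + 13 × 4 = 322 classes (planned: 340). That is 450 pupils fewer, or 5.3%. Since 27 and 13 are both odd, neither school type divides equally: 14 + 6 against 13 + 7 schools, for example, gives 4100 against 3950 pupils.

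| Reduction | Power, class effects redrawn | Power, class effects constant |
|---|---|---|
| 25% | 84.7% | 95.2% |
| 20% | 64.7% | 81.3% |
| 15% | 40.4% | 55.5% |

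A Monte Carlo check of the revised mix at 25% gave 88.7% (150 runs, standard error about 2.6 points), which cannot be told apart from either 84.7% or 86%. The change of mix costs about 1.8 points; the choice of effect size costs about 20 to 44.

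**The case against.** The strongest reply is that the calculation is sound and its source is disclosed. Sample size {14} names OBPP as the basis of its assumptions, and the background gives OBPP's 25%. The methods section claims only a loose orientation on the meta-analyses. The background sentence giving 15 to 20% also carries a different citation from the one in the methods section, although its paragraph presents the figure as the overall result of that meta-analytic work. The Discussion already warns that changes may not be significant after one or two years. And power at 15 to 20% depends on an unstated assumption about class effects.

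Much of this stands. It narrows the point to two sections that name different sources for one quantity, and it calls for a range on the recalculated power. It does not remove the conflict: on either class-effect assumption, power at 15 to 20% is well below power at 25%.

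Some stronger readings are tempting but not supported:

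- *That 8500 and 86% are calculation errors.* Both follow from their stated inputs, and Recruitment {15} openly reports the change of mix. Nor is 8050 the achieved size: 13 is a target, the final primary count is not stated, and classes per school and class size are planning values.
- *That every pupil must answer at both waves.* The primary model has school and class effects and no pupil level. Linking pupils by code is needed only for the fourth objective.
- *That non-participation invalidates the calculation.* The text does not say whether 25 per class means enrolled or responding pupils, and it gives no participation rate. Any such rate would be an assumption.
- *That the 15% baseline is wrong because the background quotes 8.3% for Germany.* That is a survey victimization rate. The trial outcome covers direct, indirect and cyberbullying over six months, and the planning assumptions were matched to OBPP data.

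**Conclusion.** The point holds as an inconsistency in the source and size of the expected effect. The 86% is right for a 25% reduction. It is not the power for the 15 to 20% that the protocol reports from the meta-analyses to which it ties its expectation. There, with 8500 pupils, power is about 67% (at 20%) and 42% (at 15%). This rests on a two-sided 5% test and on class effects redrawn at each wave, the assumption that reproduces the stated figure. Constant class effects would raise these to about 83% and 58%, but would put power at 25% at 96%, against the stated 86%. That the 25% is a two-year result, set against a one-year main endpoint in the abstract, makes it less secure as the T1 assumption.

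The outdated school mix is a minor consistency correction: about 8050 pupils in 322 classes at the revised target, and 84.7% power at 25%.

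A reader might infer that the trial needs more schools. The documents do not support that: school recruitment is closed, and what needs correcting is the description of power.

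**What to change.** - In Statistical methods {20a}, reconcile the source of the expected effect with Sample size {14}: say that the 25% used for power is the two-year OBPP figure and that the meta-analytic range is 15 to 20%.
- In Sample size {14}, keep the original calculation as the planning basis and add power for the 27 + 13 mix at 15%, 20% and 25% (about 40%, 65% and 85%). State how class effects were treated across the two measurement points, and whether 25 per class means enrolled or responding pupils. Label any participation rate as an assumption.
- Update the Abstract, Study setting {9}, Sample size {14} and the Discussion to the revised mix, giving about 8050 pupils at the revised target in place of 8500 and 4250 per group, or the actual counts once known.
- Do not enrol more schools.

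The cost is a text revision. Design, data collection and analysis stay as they are; the stated power becomes less favourable. It is best done before results are reported, so that a non-significant T1 finding is read against the right power.

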### Recruitment {15}

The recruitment of secondary schools started in September 2021. A complete list of schools in the state of Baden-Wuerttemberg was acquired (public and private schools). For organizational reasons, only schools in two out of four regional councils in Baden-Wuerttemberg that met the eligibility criteria (912 secondary schools) were contacted by email and letter (addressed to principals and social workers). This contact contained our program flyer as well as an invitation to an information event, which took place in October 2021. In January 2022, schools received a reminder of the program by email. The step-by-step decision process of schools regarding their participation included the following: (1) Interested schools receive our detailed information folder, (2) followed by a digital meeting of a member of our research team with the school management and prevention team to clarify questions, and (3) a program presentation by a member of our research team at one of the school’s teacher conferences. In the end, teachers had to vote on the participation of their school in the program. In case of a positive vote, schools signed a participation agreement and were randomized to one of the two experimental conditions. Recruitment of secondary schools was stopped in December 2022 in order to stay within the timeline. Out of the targeted 30 secondary schools, 27 schools were recruited. Since three schools were missing, the number of primary schools was increased by three schools, resulting in a target of 13 primary schools. Thus, the overall target number of schools remained at 40.

Recruitment of primary schools started in September 2022 following an analogue approach. Four hundred and fifty-seven eligible primary schools (principals and social workers) were contacted by email and letter and invited to an information event, which took place in November 2022. Furthermore, 10 primary schools that belonged to a secondary school which already participated in the program were informed about the opportunity to join the program as well. In January 2023, the primary schools received a reminder of the program by email. Inclusion of primary schools was stopped in September 2023.

Recruitment of participants began in June 2022 and will be completed by October 2025.

## Assignment of interventions: allocation

### Sequence generation {16a}

Whole schools were randomly assigned to either IG or CG based on a Randomized Complete Block Design. Even though cluster randomization should only be used when necessary and randomization at the lowest possible level is recommended [40], an alternative randomization strategy was not conceivable due to the whole-school approach underlying our program. Although the program is a complex intervention with components delivered at multiple levels (including individual and class level), substantial components are delivered at the level of the cluster (school). To minimize the disadvantages of this randomization strategy, we followed the guidelines for conducting a cluster randomized trial [40] wherever possible. For example, we allowed for clustering in the sample size calculation as well as in the analysis (see Sect. 14), specified the target of inference (the typical individual) and kept recruiters (class teachers) masked to the cluster allocation (at least at baseline). Furthermore, randomization was automatically performed via a predefined algorithm, stratified by three school types (primary schools = *Grundschule*: grades 1 through 4; A-level schools = *Gymnasium*: comparable to high schools for grades 5 through 12 or 13, more academic, required for enrolment at university; B-level schools = *Realschule/Werkrealschule/Gemeinschaftsschule*: comprises part of general or practical high school education, generally for grades 5 through 9 or 10, allows for the option to commence vocational training, but is insufficient for enrolment at university). This procedure ensured that there was approximately the same number of schools per school type in each group.

